## **8.2 Randomisation, blinding and treatment allocation**

### **8.2.1 Process of randomisation**

Participants will be allocated in the EDB group or endolymphatic sac decompression group using an automated telephone randomised service provided by Castor. Participants will be stratified according to gender and duration of MD (recent-onset versus mature MD participants). A “recent-onset MD participant” is defined as having their first MD vertigo attack in the last two years prior to inclusion. “Mature MD participants” have had their first MD vertigo attack more than two years prior to inclusion. By stratification for the duration of the disease, the effect of the natural course of disease on the outcome is reduced.

The two ear surgeons will be present up to wherein the sac is completely skeletonized. Then one of the surgeons will leave the OR. The randomisation for clip or decompression

operation will be performed using the automated telephone randomised service. The surgeon who leaves the OR will take care of the follow up and does not know whether the clip has been placed or not.

### **8.2.2 Blinding of randomisation and follow up**

The ENT surgeon responsible for follow up will be blinded as he/she has left the OR when randomisation and possible clipping took place. The ENT surgeon will be blinded until debinding at 1-year follow up of the last patient.

The coordinating investigator will take care of the follow up of the patients in the HagaHospital and will be blinded for these cases.

The patient will be blinded until the last patient is followed up for 1 year.

### **8.2.3 Emergency unblinding**

Emergency unblinding may occur in the following situations:

- In case of a medical emergency where knowledge of the blinded treatment is necessary
- For the treatment of (serious) adverse event
- If requested by the Safety Committee.

The investigator must document the action taken and promptly notify the sponsor. Code breaks should only occur in exceptional circumstances as mentioned above and if it is absolutely essential for further management of the patient.

## **8.3 Study procedures**

Throughout the trial, all data will be collected in Castor Electronic Data Capture (EDC). The handling of personal data will be in compliance with the Dutch General Data Protection Regulation (in Dutch: Algemene Verordening Gegevensbescherming (AVG)).

### **8.3.1 Preoperative procedures (T-1)**

All PCs will be visited by the coordinating investigator ([name]) for explanation about informing patients. A handout with information will be issued. This makes sure collection of data will be executed in a uniform and reproducible manner. Moreover, all principal investigators at each study site will be instructed which adverse events can be expected, how to inform the participants about the adverse events and how to process serious adverse events in both the eCRF and toetsingonline.nl (this is in line with the in the Ethical Committees guidelines in the Netherlands). All vertigo patients in the participating centres are registered, the fraction of Ménière's patients is noted, the fraction of Ménière's patients approached for participation is registered. This data is needed for generalisability.

Lastly, the data management system (Castor EDC) will be demonstrated and main investigators will fill out a questionnaire regarding their expectations of the trial.

PCs will assess patients for eligibility for the study using the inclusion and exclusion criteria. Once a patient has agreed to participate and has signed informed consent, a new record will be created in Castor by the coordinating researcher. Baseline characteristics, defined as the last valid values prior to study start or protocol initiation procedure, will be registered.

Baseline characteristics that are entered into Castor:

|                        |                                                       |                                                |
|------------------------|-------------------------------------------------------|------------------------------------------------|
| Demographic data       | Age                                                   | Years                                          |
|                        | Gender                                                | M/F                                            |
|                        | Length                                                | Cm                                             |
|                        | Weight                                                | Kg                                             |
|                        | BMI                                                   | kg/m  (calculated)                 |
| Ménière's disease      | First attack                                          | dd-mm-yyyy                                     |
|                        | Duration of MD                                        | Days (calculated)                              |
|                        | Most recent attack                                    | dd-mm-yyyy                                     |
|                        | Mean number of attacks per month in the last 6 months | Number                                         |
|                        | Previous treatments                                   | None
Betahistine
Intratympanic injection |
|                        | Number of sessions IT injections                      | Number                                         |
|                        | Number of IT injections                               | Number                                         |
|                        | Substrate of IT injections                            | Dexamethason
Kenacort
Solumedrol         |
| Comorbidities          | All                                                   | (Free text)                                    |
| In-/exclusion criteria | Meets in- and exclusion criteria                      | Yes/no                                         |
| Attacks                | Number of attacks in the past 6 months                | Number                                         |
|                        | Number of attacks in the past 2 months                | Number                                         |
| Informed consent       | Informed consent obtained?                            | Yes/no                                         |
|                        | Date of informed consent                              | dd-mm-yyy                                      |
|                        | Version of IC-form                                    | Free text                                      |

| Physical examination | vHIT                  | Gain left/right                                                  |
|----------------------|-----------------------|------------------------------------------------------------------|
|                      | Weber                 | No lateralization
Lateralizes to left
Lateralizes to right |
|                      | Rinne right           | Positive
Negative                                             |
|                      | Rinne left            | Positive
Negative                                             |
|                      | Dix Hallpike          | Positive
Negative                                             |
|                      | If positive: side:    | Left
Right                                                    |
|                      | Diadochokinesis       | Normal
Abnormal                                               |
|                      | If abnormal: side     | Left
Right                                                    |
|                      | Eye pursuit movements | Smooth
Abnormal                                               |
|                      | If abnormal: direct   | Left
Right
Up
Down                                      |

An MRI- and CT-scan will be performed and the patient is referred to a vestibular therapist. A PTA, vHIT and calorigram will be performed. Moreover, from the moment of inclusion, the patients starts reporting in de DizzyQuest App. This is a daily questionnaire of 31 questions addressing general functioning. In case of an attack, a short questionnaire is to be filled out. The inclusion and exclusion criteria will be double-checked by the coordinating investigator and if the patient does meet the criteria, the first survey package is sent through email. This survey pack consists of the HADS, DHI, THI, SF-36, EQ-5D VAS, NPQ, VADL, VAP and a questionnaire about expectations of the treatment.

All the pre-operative data is entered in Castor.

 The VAP and VADL are newly developed questionnaires to assess the effect of dizziness and/or balance problems on patients' ability to do things. They are not an outcome measure in this study, but we aim to anticipate on the possibility that the Bárány Society takes the outcomes of questionnaires into account in future studies. These questionnaires are taken for this trial as well, to enable comparison of the results of this study in the future that only use the VAP and the VADL.

In the following weeks, the patient visits the vestibular therapist, who takes the medical history and performs the first measurements. The patient is seen by the anaesthetist for regular pre-operative screening.

The MRI, PTA, vHIT, calorigram and vestibular therapy are regular medical treatment. The CT-scan, reporting the DizzyQuest App and questionnaires are extra for this study. No diagnostic procedures will be postponed due to participation in this trial.

### **8.3.2 Surgical procedure (T=0)**

Surgery takes place either at the site of inclusion, or in the HagaHospital. This depends on preference of the local researcher, and availability of equipment at the site. If surgery is performed at the HagaHospital, the local researcher (who has included and will follow the patient) is welcome to join the surgery. An experienced ENT-surgeon who has performed at least 20 EDB procedures ([name]) will always attend surgery to ensure there are not intraoperative differences that may induce differences in outcome. Moreover, this facilitates blinding of the follow-up surgeon.

The surgical procedure is described in chapter 5 'Treatment of participants', 5.1

Investigational product, subheading 'surgical procedure in EDB group'. The randomisation for a clip or decompression operation will be performed using the automated telephone randomised service from Castor. The outcome of randomisation and placing of clip (only EDB) will be documented in Castor. For the purpose of 'implantenregistratie', all used clips and their LOT-number must be documented. Normally, this registration takes place in the electronic patient files, but for blinding purposes, this will now be documented in a paper notebook. After completion of the trial and debinding, this information will be added to the electronic patient file.

An interim analysis of the data for the first 21 participants 6 weeks after surgery will be performed. The DSMB will assess the results and discuss the outcome, and give advice whether or not to continue the study.

### **8.3.3 Postoperative procedures**

- One week after surgery (T+1)

One week after surgery, the patient will visit the ENT-surgeon for regular post-operative care. A vHIT will be performed. Moreover, the patient will visit the vestibular therapist whom will commence treatment. A balance test, dynamic visual acuity and gait analysis will be performed. Exercises that should be performed at home by the patient are explained. In the

following weeks, the patients carries these exercises out at home, and visit the vestibular therapist three times with two weeks in between the visits.

As surgery is currently not a normal medical treatment, this visit and these measurements are all extra for this study.

- Three months after surgery (T+2)

At three months after surgery, a follow up visit is planned at the ENT-surgeon. A vHIT is performed. The patients visits the vestibular therapist who performed measurements who finishes treatment and performs measurements. An MRI-scan and PTA are performed. The patients receives a survey package through email, consisting of the DHI, THI, FLS, EQ-5D VAS, SF-36, iMCQ and iPCQ.

This visit and these measurements/tests are all extra for this study.

- Six months after surgery (T+3)

At six months after surgery, a follow up visit is planned at the ENT-surgeon. A vHIT is performed. The vestibular therapist performs measurements. A PTA is performed. The patients receives a survey package through email, consisting of the DHI, THI, FLS, EQ-5D VAS, SF-36, iMCQ and iPCQ.

This visit and these measurements/tests are all extra for this study.

- Twelve months after surgery (T+4)

At twelve months after surgery, the last follow up visit for this trial is planned. A vHIT is performed, as well as a PTA, an MRI-scan and calorigram. The vestibular therapist performs measurements and the patients receives a survey package through email consisting of the DHI, THI, FLS, EQ-5D VAS, SF-36, iMCQ, iPCQ, VADL and VAP. If the patient was in de EDB-group, a CT-scan will be performed to assess if the clip is in place in the patients still suffers attacks. If results are in favour of EDB, and patients still suffer attacks, the patients in the decompression group will be offered EDB surgery.

This visit and these measurements/tests are all extra for this study.

### 8.3.4 Flow chart

A simplified flowchart can be found here. For the more specified flow chart, see Appendix 2.

[figure not shown]

#### **8.4 Withdrawal of individual subjects**

Participants can leave the study at any time for any reason if they wish to do so without consequences. The investigator can decide to withdraw a patient from the study for urgent medical reasons.

#### **8.5 Replacement of individual subjects after withdrawal**

The number of participants (as mentioned in chapter 3) takes into account that at least 15% of the participants in both arms of the study will drop out. We therefore do not expect to replace participants.

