#### 4.4 Sample size calculation

The sample size for this RCT was computed using software package PASS 11. The sample size calculation is based on the study performed by Saliba (Saliba 2015), in which complete control of vertigo was reached in 96,5% of the patients who underwent EDB. According to literature, endolymphatic sac decompression is effective in  $\pm 70\%$  of the patients (Brinson 2007, Convert 2006, Durland 2006).

We compare MD participants undergoing an operation with clip (EDB group: A group) independently with MD participants undergoing operation without clip (decompression group: B group). Null hypothesis is that the percentage points difference between groups is nil ( $p_A = p_B$ ), with two-sided alternative hypothesis ( $p_A \neq p_B$ ) and with anticipated 25% percent difference ( $p_A = 95\%$  and  $p_B = 70\%$ ). Power is at least 80%. The chance of a false positive finding for either of the analyses is controlled at the 5% level (family wise error rate). To obtain a power of at least 80% for Fisher's Exact test, the required sample size is 32 in groups A and B (allocation ratio = 1). Loss to follow-up will likely occur in a small percentage of cases ( $n=5$  per arm). No selective loss to follow-up is anticipated and a missing-at-random assumption seems reasonable. Missing outcomes will therefore be imputed using multiple imputation in the main analysis. Two sensitivity analyses will be conducted as well, where missing outcomes will be treated as failures or success, respectively. In this case the sample size would be 37 in group A and B (allocation ratio = 1). The total number of participants would be 74.

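### Section 8.5 claims an allowance of at least 15% drop-out per arm, but the sample size in section 4.4 covers 5 of 37, or 13.5%

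*Protocol*

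**What the plan says.** Section 8.5 of the protocol states that the number of participants "takes into account that at least 15% of the participants in both arms of the study will drop out". It draws a consequence directly from this: "We therefore do not expect to replace participants". For the number itself it refers the reader to chapter 3.

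The number is derived in section 4.4, which requires 32 per arm for the primary comparison. It continues: "Loss to follow-up will likely occur in a small percentage of cases", put at five per arm. It then concludes: "In this case the sample size would be 37 in group A and B", and "The total number of participants would be 74". No calculation in the protocol uses 15%. Chapter 3 (study design) describes duration, centres and the choice of control, and gives no number of participants.

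Three other places bear on what a drop-out costs the analysis:

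- Section 4.4 plans multiple imputation of missing outcomes in the main analysis.
- Section 8.6 asks for at least the primary outcome to be obtained after withdrawal of consent, where permitted, and uses data collected up to that point.
- Section 10.1.1 excludes a participant only when all primary outcome data are missing, and says the sample size was corrected for this.

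**The concern.** Two sections describe the same allowance with different figures. Section 4.4 can absorb at most 5 losses among 37 enrolled per arm. Section 8.5 says that 15% is covered and calls it a minimum. The two cannot both be right if the percentage refers to the participants in each arm, which is how section 8.5 words it.

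This matters because section 8.5 uses the percentage as its reason for not expecting to replace anyone, and section 10.1.1 also leans on the allowance. An ethics committee or monitor reading section 8.5 would take it that a loss of 15% or more per arm leaves the required number intact. By the protocol's own figures it does not, although the gap is small. The pointer to chapter 3 means that a reader cannot readily check the claim.

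**Working it through.** **Inputs.** Required per arm: 32 (section 4.4). Allowance for loss: 5 per arm (section 4.4). Enrolled: 37 per arm, 74 in total (section 4.4). Drop-out said to be covered: at least 15% per arm (section 8.5).

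**1. Reproducing the plan's figure.** 32 + 5 = 37 per arm, and 2 x 37 = 74. The enrolment figure follows exactly from the inputs of section 4.4.

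**2. The allowance as a percentage.**
- Of those enrolled: 5/37 = 13.5%.
- Of those required: 5/32 = 15.6%.

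Only the second exceeds 15%. Its denominator is the number meant to remain, not the number who can drop out.

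**3. What 15% leaves.**
- Per arm: 37 x (1 - 0.15) = 31.45, against 32.
- In total: 74 x (1 - 0.15) = 62.9, against 64.

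**4. Whole participants.**
- 5 losses: 5/37 = 13.5%, leaving 32.
- 6 losses: 6/37 = 16.2%, leaving 31.

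Exactly 15% of 37 is 5.55 and cannot occur in a single arm. A count of 31 therefore belongs to a loss of 16.2%.

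**5. What 15% would need.** n / (1 - d) = 32/0.85 = 37.65, i.e. 38 per arm or 76 in total, against 37 and 74. Multiplying instead of dividing gives 32 x 1.15 = 36.8, which rounds up to 37. This may be how the 15% arose.

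**6. Effect on power.** Exact enumeration of a two-sided Fisher's test at 5%, with 95% versus 70% attack-free, gives 68.0% power at 32 per arm and 65.6% at 31. Losing one more observed outcome per arm costs 2.4 percentage points.

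**The case against.** The strongest defence is that 15% is the same allowance on another base: 5/32 = 15.6%, which is indeed at least 15%. That is probably where the figure came from, though the protocol does not show it. It explains the slip but does not rescue the sentence, because section 8.5 speaks of participants in the arms who drop out, and those come from the 37 enrolled. It does mean that the design is not without an allowance; the allowance is expressed on the wrong denominator.

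The second defence is that drop-out is not the same as leaving the analysis, and this stands. Missing outcomes are to be imputed, outcomes are sought after withdrawal, and only a participant with no primary outcome data at all is excluded. A reader might infer that at 15% drop-out the trial necessarily ends with 31 analysed per arm, below its requirement. The documents do not support that: 31 is the count at 16.2%, and a sixth drop-out in an arm may still contribute an outcome.

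A reader might also infer that the protocol forbids replacement and so locks the shortfall in. Section 8.5 states an expectation, not a prohibition.

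Finally, the gap is 37.65 against 37. That is fair, and it is why the point is minor.

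**Conclusion.** Wrong as written, and minor. The number of participants allows for a loss of at most 13.5% of those enrolled per arm, not at least 15%, and the cross-reference to chapter 3 leads nowhere. At 15% loss of outcome, 31.45 per arm would be observed against 32 required, a shortfall of 0.55 of a participant per arm.

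This rests on two assumptions. The percentage in section 8.5 is read as a share of the participants enrolled in each arm, which is its natural meaning. The requirement of 32 is taken at face value as the number with an observed outcome. Whether 32 per arm delivers the 80% power claimed for Fisher's exact test is a separate question: the exact calculation above gives 68.0%. The mismatch between sections 4.4 and 8.5 is there whichever base number is right. Nothing here shows that the trial is materially undersized because of drop-out, or that the expectation of no replacement has to change.

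**What to change.** Replace the first sentence of section 8.5 with: *The number of participants (section 4.4) allows for loss to follow-up of 5 of 37 participants per arm (13.5%).* Keep the sentence that follows: "We therefore do not expect to replace participants". This also corrects the cross-reference from chapter 3 to section 4.4. In section 4.4, put 13.5% beside the five per arm so that both sections carry the same figure.

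The cost is wording only. There is no extra enrolment and no change to the replacement expectation, the analysis or any procedure. The stated allowance becomes slightly less favourable.

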#### **8.6 Follow-up of subjects withdrawn from treatment**

A participant may be excluded from the study prior to the expected protocol completion for safety reasons, failure of subject to adhere to protocol requirements, or subject consent withdrawal. Since early withdrawal could be related to the surgery, it is of great importance to analyse these final data for the integrity of the study. If a participant withdraws consent to continue follow up participation, attempts should be made to obtain permission to record at least primary outcome data. The participant will be contacted by phone and email, the next-of-kin will be contacted, a letter asking to contact us will be send or the patient's general practitioner will be contacted.

If a participants withdraws its consent, he/she is allowed to do so without further explanation. If this is the case, participants should contact the ENT-surgeon who takes care of follow up. This ENT-surgeon then contacts the coordinating researcher. The data that were collected until the moment of consent withdrawal, will be used in the analyses.

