## 10. STATISTICAL ANALYSIS

Statistical Data analysis of the study data will be performed using SPSS (version 17.0). All analyses will be performed through Intention to treat.

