#### 10.1.1 Imputation of App-recorded data

The daily questionnaire taken via the DizzyQuest app is likely to contain missing data. All other missing data will be labelled 'NAmissing' in SPSS. Multiple imputation will be used to create complete data sets. Depending on the missing data pattern different strategies will be followed.

Imputation variables are base line measurements, time-course measurements and daily App-data.

- Missingness  $\leq 10\%$

If little data is missing, the data will be treated as one data-row per patient (wide format).

In this case, information for imputing missing values will be taken from the exact same time points of other patients. This strategy can account for possible time trends.

- Missingness  $> 10\%, \leq 50\%$

If more data is missing, the data of each patient will be split into one row per day (long format), when the previous 10 days will be included in each row. After imputation, the previous days will be removed to avoid duplication of data. This strategy includes information on missing data across time periods and can lead to wrong imputations for time trends longer than 10 days.

- Missingness  $> 50\%$

The same strategy as for missingness between 10% and 50% is followed except for including a smaller time window. 10 previous days will be used. If all primary outcome data are not available (missing), the participant will be excluded from the analyses. The a priori sample size estimation has been corrected for this.

The above cut-offs and time ranges reflect expectations. Actual values will be selected based on the variability of imputed values.

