#### **12.6.1 Data analysis and release of results**

The data from the trial will be centrally analysed from Participating Centres by the trial statistician.

We plan to use non-parametric tests in the analysis of the data. Non-parametric methods are more robust as they make fewer assumptions (distribution of the data). As a downside non-parametric are less efficient, i.e. they need a higher sample size to achieve the same power. As a compensating factor we use the relative efficiency of the Mann-Whitney U-test as compared to the t-test which has been estimated as 95% (Conover 1999, Practical Nonparametric Statistics).

In order to estimate a realistic treatment effect that avoids bias due to treatment-arm crossover and selective drop-out, an intention-to-treat analysis will be conducted as the primary analysis.

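### Section 8.6 allows exclusion for non-adherence but secures the 12-month outcome only for participants who withdraw consent

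*Protocol*

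**What the plan says.** **Leaving the study.** Section 8.6 gives three grounds. The first two stand in one clause, under which someone in the trial "may be excluded from the study prior to the expected protocol completion for safety reasons, failure of subject to adhere to protocol requirements". Withdrawn consent is the third. Section 8.4 gives participants the right to leave and then says: "The investigator can decide to withdraw a patient from the study for urgent medical reasons". It does not mention non-adherence.

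**Outcome data after leaving.** Section 8.6 states an aim that covers all early exits: "Since early withdrawal could be related to the surgery, it is of great importance to analyse these final data for the integrity of the study". The two operative instructions are narrower. One reads "If a participant withdraws consent to continue follow up participation, attempts should be made to obtain permission to record at least primary outcome data", and it is followed by the contact routes (telephone, email, letter, next of kin, general practitioner). The other reads "The data that were collected until the moment of consent withdrawal, will be used in the analyses".

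**Analysis.** Section 10 says "All analyses will be performed through Intention to treat", and section 12.6.1 says that "an intention-to-treat analysis will be conducted as the primary analysis", giving avoidance of bias from selective drop-out as one reason. Section 4.4 handles missing outcomes by multiple imputation under missing at random, with sensitivity analyses that count them all as failures or all as successes. Section 10.1.1 adds: "If all primary outcome data are not available (missing), the participant will be excluded from the analyses".

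**The concern.** Randomisation takes place during surgery (sections 5.1 and 8.2.1), and the allocated treatment is complete when the patient leaves theatre. What a patient can then fail to adhere to is mostly the measurement and support programme: the daily app, visits, questionnaires and rehabilitation. The primary outcome is itself derived from the app (section 10.1.2). Excluding a patient for poor adherence after surgery therefore ends the collection of the very outcome that the trial needs.

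The result is lopsided. A patient who withdraws consent is to be approached for at least the primary outcome. A patient who has refused nothing, but whom the team excludes, has no stated follow-up. Keeping up a 31-question daily form for a year plausibly depends on how the patient is doing. If so, exclusion on this ground selects on outcome and could fall unevenly on the arms.

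**Working it through.** **Step 1: exit grounds against outcome provisions.**

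| Ground in 8.6 | Also named in 8.4? | Primary outcome pursued (8.6)? | Use of collected data stated (8.6)? |
|---|---|---|---|
| Consent withdrawal | Yes (participant's right) | Yes | Yes |
| Safety | Yes, as urgent medical reasons | Not stated | General aim only |
| Non-adherence | No | Not stated | General aim only |

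The general aim of analysing data from early leavers covers all three rows. The means of obtaining 12-month data covers only the first.

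**Step 2: what happens to such a patient in the analysis.** Nothing in 8.6 removes anyone from the analysis. With some app data, the patient falls under the imputation tiers of 10.1.1. With all primary data missing, 10.1.1 drops the patient, whereas 4.4 would impute. That last step is the one that conflicts with section 10. For a patient who stops part-way, the text does not settle whether 10.1.1 imputes or drops.

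**Step 3: the plan's own figures.** 32 + 5 = 37 per arm and 2 × 37 = 74, which reproduces section 4.4. The loss allowance is 5/37 = 13.5%.

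Exact power = Σx Σy Bin(x; 37, 0.95) · Bin(y; 37, 0.70) · 1[two-sided Fisher p ≤ 0.05].

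At 37 per arm this is 77.6%, the baseline used below. At 32 per arm it is 68.0%, so the stated 80% for Fisher's test is not reproduced. Uncorrected chi-square at 32 gives 80.6%. That is a separate matter and does not affect this point.

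**Step 4: illustration.** The number and pattern of exclusions are assumptions; the documents give none. No imputation is applied.

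*Failures lost from the control arm only.* Expected control successes are 0.70 × 37 = 25.9, about 26.
- Four lost: 26/37 = 70% becomes 26/33 = 79%, and the 25-point difference becomes 95 − 79 = 16 points.
- Two lost: 26/35 = 74%, a shift of 4 points.

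| Control failures lost | Exact Fisher power (95% v 70%) |
|---|---|
| 0 | 77.6% |
| 1 | 77.6% |
| 2 | 68.0% |
| 4 | 50.6% |

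These values remove the failures inside the enumeration. Treating the four-loss case instead as a fresh trial of 37 v 33 at 95% v 79% gives 48.8%, hence a range of 49-51%.

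*Failures lost from the EDB arm only, true rate 70% in both arms.*

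| EDB failures lost | Shift in difference | Type I error (two-sided Fisher) |
|---|---|---|
| 0 | 0 | 2.9% |
| 1 | +1.9 points | 4.3% |
| 2 | +4.0 points | 6.2% |
| 3 | +6.2 points | 9.5% |

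The distortion can therefore run in either direction.

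**The case against.** A reader might infer that the clause contradicts intention to treat and removes randomised patients from the analysis. The documents do not support that. Leaving the study is not leaving the analysis; 8.6 itself stresses analysing early leavers; 4.4 imputes missing outcomes and brackets them with failure and success analyses; and 10.1.1 drops a participant only when all primary data are missing. The clash between 4.4 and 10.1.1 exists whatever the reason for the loss.

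A reader might also infer that missed app entries trigger exclusion. No section says so. Section 12.1 responds to missed questionnaires by contacting the participant, and people unable or unwilling to use the app are screened out in section 4.3. The clause also covers the period between inclusion and surgery, where exclusion precedes randomisation and no intention-to-treat question arises. Patients are blinded, so any difference between arms would come indirectly, through outcome. The five losses per arm are there to absorb early exits, so using them is not a further harm.

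All of this stands, and it narrows the point. What survives is that 8.6 states a ground for ending follow-up of treated, randomised patients and gives no means of obtaining their outcome. Imputation is a weaker remedy than a telephone call. Section 4.4 assumes missing at random and no selective loss, which exclusion for poor app use may break. Section 10.1.2 expects missing app data to be imputable as attack-free, so a partly observed patient could tend to count as a success.

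**Conclusion.** The point holds as a gap and an inconsistency in the withdrawal rules. Section 8.6 permits exclusion for non-adherence without continued outcome collection and does not match 8.4. Through 10.1.1 it can, in the fully missing case, take a randomised patient out of an analysis declared as intention to treat. The clause alone is not a breach of that principle.

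The size cannot be estimated from the documents. The figures above assume that every excluded patient is a failure, that all come from one arm, and that nothing is imputed. On those terms a single exclusion leaves power unchanged at 78%, two reduce it to about 68%, and four to about 49-51%. With no true difference, two EDB failures lost raise the type I error from 2.9% to 6.2%. These are extremes, not forecasts. They show only that, with 37 per arm, a handful of avoidable outcome-related exclusions could matter. Correction is worthwhile mainly because it is cheap.

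**What to change.** 1. In 8.6, for randomised participants, remove non-adherence as a ground for leaving follow-up. State that someone who stops the app, visits or rehabilitation remains in the study for outcome assessment.
2. Extend the contact routes already listed in 8.6 so that attack status at 12 months is sought from every early leaver who has not refused, whatever the reason for leaving. Apply the sentence on use of collected data to all grounds.
3. State that all randomised patients are analysed in their allocated arm, with missing outcomes handled as in section 4.4, and bring the removal rule in 10.1.1 into line with this.
4. Reconcile the withdrawal grounds in 8.4 and 8.6.

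The cost is protocol wording and a telephone contact for a few patients. The sample size and surgical procedures are unaffected.
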